#### Secondary outcome measure

Psychosocial well-being (health-related quality of life) and pain coping, cognitions and self-efficacy are of clinical relevance and represent the secondary outcomes. All secondary outcomes are assessed by validated questionnaires as self or proxy reports.

#### Heath-related quality of life

Health-related quality of life (HRQoL) is assessed by the German version of the Pediatric Quality of Life Inventory. (PedsQL; [35]). This 23-item questionnaire covers four dimensions of HRQoL (physical, emotional, school, and social). This measure showed sufficient to good internal consistency in previous studies (α = .68 to α = .80; [20, 21]). In addition, we assess the child’s pain-related quality of life by the illness module of KINDL^R^
[36], which covers six items. Children are to rate the degree of difficulties for each item on a five-point scale (never to almost always). HRQoL will be assessed in both the child and parent report.

#### Pain - related coping and cognitions

Pain-related coping will be assessed by the German version of the Pediatric Pain Coping Inventory (PPCI-revised; [37, 38]). The questionnaire includes three subscales of behavior-related coping strategies when the child is in pain: passive pain coping (for example, ‘I go to bed’ (10 items, α = .68)), seek for social support (for example, ‘I have my mother, father or a friend sit with me’ (8 items, α = .80)) and positive self-instruction (for example, ‘I tell myself to be brave’ (7 items, α = .63)).

#### Self-efficacy

For assessing child’s pain-related self-efficacy, we use the self-efficacy scale by Bursch [39]. Children are asked to rate how sure they are to pursue everyday activities when they are in pain (for example, ‘make it through a school day’ or ‘be with your friends’) on a five-point scale (very sure to very unsure). This seven-item measure showed good internal consistency in the validation study (α = .80; [39]).

#### Predictors

In addition to the confirmatory aspects of this trial, further child- and parent-related variables will be assessed for analyzing predictive or moderating influences on treatment effects. Child and parental strain will be analyzed with respect to their impact on treatment outcome.

Further, the amount of healthcare utilization and school attendance will be assessed at baseline and during follow-up.

#### Points of measurement

Applying an observer-blind design, data are collected by questionnaires for children and parents at four points of measurement. Pre-intervention (T1) and postintervention (T2) will take place at the study centers. As the primary outcome is assessed by a pain diary over 14 days, T1 and T2 are located 14 to 21 days before and after the intervention phase. Follow-up assessment will take place 3 (T3) and 12 (T4) months after intervention, also including pain diaries and questionnaires for child and parents. Follow-up data will be collected via mail by the University of Potsdam.

The issue of concomitant care and use of other medical or psychological services is included in patient information prior to study inclusion. The families are not to utilize other therapeutic approaches for FAP such as pain medication or other treatments. Due to ethical reasons, medical or psychological consultations are not prohibited during the follow-up time span. Data on the consultation rate are included in the follow-up survey.

### Sample size - power analysis

The calculations rely on the high effect size of our primary outcome (d = 1.09 for the composite pain score; see [21, 22]) and correlation among repeated measures 0.8 (see [20–22]). Since our recent single-site study included a 3-month follow-up and a waiting list control group (instead of an active control group [21, 22]), power analysis for the primary outcome is based conservatively on a medium effect size (f = 0.25; d = 0.6). Independent variables are intervention (2), gender (2), age (2) and site of intervention (5), forming a total of 2^3^*5 = 40 groups.

In the study centers, n = 450 children will be assessed for eligibility and a total number of n = 112 children will be allocated to the trial (n = 56 in IG, n = 56 in CG). We assume a drop-out rate of 20% [cf. 18], resulting n = 112 children to be analyzed in the intention-to-treat analysis (ITT) and n = 90 children for the per protocol analysis (PPA).

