### Primary analysis of the primary endpoints

An analysis of covariance will be performed in the ITT population, comparing the log area under the pain intensity curve from intervention to 12-month follow-up between the two random groups adjusted for the baseline measurements. Length of pain episodes will be analyzed analogously. Frequencies will be analyzed using a Poisson regression model.

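### The planning effect size is given as f = 0.25 and d = 0.6, which are different assumptions for two equal arms, and the 40-group layout behind the power analysis is not the planned primary model

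*Protocol article*

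**What the plan says.** The section on sample size and power starts from an earlier result, "d = 1.09 for the composite pain score", and a "correlation among repeated measures 0.8". Because the earlier study had a waiting-list control and a 3-month follow-up, the section then falls back on a "medium effect size (f = 0.25; d = 0.6"). It describes the design this way: "Independent variables are intervention (2), gender (2), age (2) and site of intervention (5"), "forming a total of 2^3^*5 = 40 groups".

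The resulting size is a "total number of n = 112 children will be allocated to the trial (n = 56 in IG, n = 56 in CG"). On losses it says "We assume a drop-out rate of 20" per cent, and reports 112 children for the intention-to-treat analysis and 90 for the per-protocol analysis. The section gives no target power, alpha or sidedness.

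The section on the primary analysis plans something different: an ANCOVA of the log area under the pain-intensity curve, comparing the two randomised groups "adjusted for the baseline measurements". The confirmatory-analysis section sets the hierarchically ordered tests at 2.5%, with an overall level of at most 5%, and does not say whether they are one- or two-sided.

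**The concern.** The article prints the two effect sizes as one assumption. With 1:1 allocation they are two assumptions, and the difference between d = 0.50 and d = 0.60 is large enough to change what 112 children can detect. Shortening a full protocol for a journal does not explain this, because both values are on the page and they disagree.

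The listed inputs (f, a correlation among repeated measures, a number of groups) are those of a repeated-measures ANOVA. The pair 112 and 90, however, looks like a two-group comparison inflated for drop-out. A reader cannot tell which calculation was done, and so cannot tell whether 112 is the number needed for analysis or the number after allowing for losses.

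The factorial layout by gender, age and site also does not describe the primary model. Gender and age appear only as adjusters in the secondary mixed model.

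**Working it through.** **Inputs from the article.** f = 0.25; d = 0.6; correlation among repeated measures 0.8; 40 groups; 112 allocated 1:1; 20% drop-out; four measurement points, three of them after treatment.

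**Assumed.** Power 80% and two-sided 5% (the same as one-sided 2.5%), because the power section states neither. No clustering.

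**Step 1: converting the effect size.** For two equal arms f = d/2.
- f = 0.25 gives d = 2 × 0.25 = 0.50.
- d = 0.6 gives f = 0.6/2 = 0.30.

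**Step 2: reproducing the article's figures with d = 0.6.** Two-sample t-test, noncentrality d × √(N/4). The smallest total N with 80% power is 90 (45 per arm): 0.6 × √22.5 = 2.846, power 80.4%. Then 90/0.8 = 112.5, and 112 × 0.8 = 89.6. This reproduces both 112 and 90. It uses neither f = 0.25, nor the correlation of 0.8, nor the 40 groups.

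**Step 3: the listed repeated-measures inputs with f = 0.25.** Between-subject treatment effect with 1 numerator degree of freedom, m measurements and N − k denominator degrees of freedom (k groups). The noncentrality is f² × N × m/(1 + (m − 1) × 0.8).

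| m | k | N for 80% power | Power at N = 90 |
|---|---|---|---|
| 3 | 40 | 112 | 70.5% |
| 4 | 40 | 110 | 71.3% |
| 3 | 2 | 111 | 71.2% |
| 4 | 2 | 109 | 72.1% |

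For m = 3 and N = 112 the noncentrality is 0.0625 × 112 × 3/2.6 = 8.08. At N = 90 it falls to 6.49. Here 110 to 112 (with 40 groups) is the number analysed. To keep it after 20% loss, 110/0.8 = 137.5 to 112/0.8 = 140 would have to be allocated.

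**Step 4: what the choice of effect size does (t-test, two-sided 5%).**

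| Effect | N = 90 | N = 112 | N for 80% power |
|---|---|---|---|
| d = 0.60 | 80.4% | 88.2% | 90 |
| d = 0.50 | 65.0% | 74.6% | 128 |

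The difference at 90 is about 15 percentage points.

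**Step 5: the effect of the 40 groups.** In Step 3, moving from 2 to 40 groups adds one child (111 to 112, or 109 to 110). There would be 112/40 = 2.8 children per cell, but a 1-df treatment contrast is barely affected.

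**Step 6: the planned model.** Baseline adjustment with correlation r between baseline and outcome multiplies the noncentrality of the F test by 1/(1 − r²). The article gives 0.8 among repeated measures but no correlation between baseline and log AUC, so r is an assumption. At the smaller effect, d = 0.50, before clustering:

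| Assumed r | N = 90, two-sided 5% | N = 112, two-sided 5% | N = 90, two-sided 2.5% |
|---|---|---|---|
| 0.5 | 77% | 86% | 68% |
| 0.6 | 83% | 91% | 75% |
| 0.8 | 97% | 99% | 95% |

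The last column shows why sidedness matters if the 2.5% in the confirmatory section is meant as two-sided.

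**The case against.** The strongest reply is that the number is sound and only a label is wrong. One stated effect size, d = 0.6, together with the stated drop-out gives both 112 and 90. The repeated-measures route also lands on 112, which the article says is the intention-to-treat number, and the primary analysis is intention-to-treat with missing values substituted. The 40 groups cost about one child. The 65% for d = 0.50 at 90 comes from an unadjusted t-test that the article does not plan. No power statement is printed, and a condensed article may leave that to the full protocol.

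Most of this stands. A reader might infer that 112 with 20% drop-out cannot follow from any single set of the stated inputs. Step 2 shows that it does, at an assumed 80% power. A reader might also infer that the trial is too small; Step 6 shows that this is not established for the baseline-adjusted model. Nor would a null result be uninterpretable, since the confidence interval shows which effects are excluded, whatever was assumed in planning.

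Two things remain. The printed equivalence is wrong whichever half was meant. And if f = 0.25 was meant, keeping 112 rows by substitution does not restore the information lost with the children who drop out, so the allowance for loss is missing from that calculation.

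**Conclusion.** The point holds as a correction to the stated sample-size basis; it is not a must-fix. The article gives two incompatible values for one assumption. If d = 0.60 was used, 112 randomised and 90 remaining are reproduced, but most of the listed inputs played no part. If f = 0.25 was used with the correlation and 40 groups, 110 to 112 is the number analysed, drop-out is not covered, and power at 90 is about 70 to 72%. The described layout is not the primary ANCOVA; that is a mismatch of description with almost no effect on the number.

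These figures rest on the assumed 80% power and two-sided 5%, and ignore any clustering from delivery in groups. The documents do not show that 112 is inadequate for the planned analysis. They leave the trial's power for that analysis unidentified.

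**What to change.** In the sample-size section:

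1. State one effect size with its matching counterpart: d = 0.50 with f = 0.25, or d = 0.60 with f = 0.30. Say which model, target power and alpha produced 112.
2. Replace the 40-group description with the planned two-group, baseline-adjusted ANCOVA of log AUC of pain intensity.
3. Report the power of that model for 112 randomised with about 90 observed, over a range of assumed baseline correlations such as 0.5 to 0.8. Use an alpha consistent with the 2.5% in the confirmatory section, and state whether it is one- or two-sided.

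Enrolment stays unchanged. The cost is a few lines of text; the restated power may be lower or higher than a reader would now assume, depending on the effect size, alpha and correlation chosen.

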#### Drop-out rate

In our pilot study we did not observe drop-out of patients. In 9 out of 10 intervention studies, drop-out rates are below 25% [18]. We assume a loss of 20% due to drop-outs during the follow-up time span (cf. [40]). To prevent selective drop-out and incomplete outcome data, all participants will be reimbursed for completely filling in the questionnaires and the pain diary in the follow-up period.

### Randomization

Allocation sequences are generated centrally at the Institute of Epidemiology at University Clinic of Hamburg-Eppendorf (KW). It will be mutually randomized in IG and CG with a 1:1 ratio. Each patient’s position on allocation sequence is defined by computer-generated random-numbers and the date of informed consent (chronologically sorted).

As groups are assigned parallel and the interventions are to be carried out mutually, blocking is dependent on the group sizes. Block sizes range between 6 and 16 patients. The total number of each block is dependent on the total number of groups to be trained. As in this trial, a maximum of 25 groups are to be trained; the number of blocks of 6 and 8 patients is restricted to five each.

The randomization procedure, in order to prevent selection bias, occurs centrally at the University of Potsdam by a person not involved in the intervention process and data analysis. We realize a stratified (according to center) block randomization. Randomization and allocation to interventions occur after assessment of pre-data and before the interventions start. Results of randomization will be provided directly only to the trainers via email (allocation concealment). Each center has to realize four different groups; at the first block of interventions, the trainer may choose the trial arm (IG versus CG); in the second block, the trainers have to change the trial arm.

The effectiveness of the randomization is evaluated post-hoc by descriptive statistical comparisons between IG and CG in known and presumed baseline predictors of treatment success (for example, pain history of the parents and socio-economic status) and relevant sociodemographic data (age and sex).

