### Blinding

The medical and psychological assessments are blinded as these precede randomization. After assignment to interventions, the outcome assessors (study nurse and site investigators) and principle investigator will be blinded. While patients and parents will be blinded, blinding of trainers in the treatment is not possible. However, trainers are not involved in the assessment process.

Group allocation will be coded by different letters; only the trainers and the administrator of randomization results will be informed about the corresponding intervention.

The primary outcome will be reported by the children themselves, who are not aware of their respective treatment allocation. Assessment of data is blinded on all points of measurement. Follow-up data will be assessed by telephone interviews (blinded interviewer) with the younger children and questionnaires for older children and the parents. Information material and questionnaires in the follow-up phase will be sent out directly to the participating families. Data collection and data analysis are independent. Data entry is operated by computer scanning and is therefore blinded.

Early unblinding is not intended. Regular unblinding occurs after complete data collection, that is, after the last data of T4 is collected and entered into data set. Process data of the intervention-specific pain diaries will be added to the data set after all other data are entered and therefore constitutes the first step of unblinding.

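### Trainers choose which arm they deliver first, so delivery order is self-selected; the second-block switch balances this only if both blocks run at similar size, and the primary model has no therapist term

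*Protocol article*

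**What the plan says.** All of the following is in the protocol article.

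- **Children (Randomization).** Allocation is 1:1, done centrally by a person who takes no part in intervention or analysis: "We realize a stratified (according to center) block randomization". On timing: "Randomization and allocation to interventions occur after assessment of pre-data and before the interventions start".
- **Trainers (Randomization).** "Results of randomization will be provided directly only to the trainers via email (allocation concealment". Then: "Each center has to realize four different groups", and "at the first block of interventions, the trainer may choose the trial arm (IG versus CG", while "in the second block, the trainers have to change the trial arm". No section randomises trainers to an arm or to an order.
- **Number and size of groups.** The Randomization section allows that "a maximum of 25 groups are to be trained", with blocks of 6 to 16 children. Intervention and controls gives 3 to 8 children per group. Stopping rules allows a centre to be closed for repeated non-adherence or low recruitment.
- **Who knows the arm (Blinding).** "only the trainers and the administrator of randomization results will be informed about the corresponding intervention". Trainers cannot be blinded but do not assess outcomes.
- **Analysis.** Primary analysis of the primary endpoints is an ANCOVA adjusted for baseline measurements. Analysis of secondary outcomes adds a mixed model with therapist as a random effect, covering primary and secondary outcomes.

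**The concern.** In a comparison of two trainer-led programmes, the skill and preference of the person leading the group can affect outcome. With ten trainers over five centres, there are about two per centre. Within a centre's first block, trainer and arm are then confounded: one trainer leads the intervention group, the other the control group, and they decide which. If the more able or more committed trainer tends to take the intervention first, the first-block contrast contains a trainer difference as well as a treatment effect.

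The compulsory switch is meant to balance this, and each trainer should deliver both arms. But the second block follows mechanically from the first, so the whole order rests on one unrandomised choice. If the second block is smaller, larger or missing, part of the trainer difference stays in the arm contrast. Order effects, such as pain-coping practice carried by a trainer into a later control group, are not balanced by chance either. The confirmatory ANCOVA as described does not separate trainer from arm.

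**Working it through.** The plan states no figure on this point, so there is nothing to reproduce. The check is a count and a bias formula.

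**Counts**
- Planned groups: 5 centres × 4 = 20, that is 10 blocks of two groups. Mean group size: 112 / 20 = 5.6.
- Groups allowed beyond the plan: 25 − 20 = 5. No trainer rule is given for a centre's fifth or later group.
- Trainers per centre: 10 / 5 = 2. This is an average; the article does not state the number per centre.

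**Formula**
Take two trainers in a centre whose children's outcomes differ by δ (in SD units). The better one leads the intervention in block 1 and control in block 2. Group sizes are a in each arm of block 1 and b in each arm of block 2.
- Share of intervention children with the better trainer: a / (a + b).
- Share of control children with the better trainer: b / (a + b).
- Bias in the unadjusted contrast: δ × (a − b) / (a + b). The sign reverses if the second block is the larger.

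**Results.** δ is an assumption; the documents give no trainer difference.

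| Group sizes, block 1 then 2 | Multiplier | δ = 0.2 | δ = 0.3 | δ = 0.5 |
|---|---|---|---|---|
| Equal | 0 | 0 | 0 | 0 |
| 8 then 6 | 2/14 = 0.14 | 0.03 | 0.04 | 0.07 |
| 8 then 3 | 5/11 = 0.45 | 0.09 | 0.14 | 0.23 |
| Block 1 only | 1 | 0.20 | 0.30 | 0.50 |

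These are values within a centre. They hold for the whole trial only if every centre has the same sizes and sorts the same way.

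**How far that is from likely**
- If equal-sized centres sort in different directions, the multiplier shrinks. With four of five one way it is (4 − 1)/5 = 0.6, and with three of five (3 − 2)/5 = 0.2. The 0.09 SD for 8 then 3 becomes about 0.05 or 0.02.
- If one centre stops after its first block and the other four run two blocks, all of equal size, the trial-wide bias is 1/9 × 0.20 = 0.02 SD.
- If the five extra groups include a third pair in two centres, each returning to its first-block order, then with equal sizes and all centres sorting alike the bias is (7 − 5)/12 × 0.20 = 0.03 SD.

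**Against the planned effect.** The sample size section uses d = 0.6. At δ = 0.2, the 8-then-3 case is 0.09 / 0.6 = 15% of it, and the first-block-only case is 0.20 / 0.6 = 33%.

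**The case against.** A reader might infer something stronger: that trainers are sent two sets of children and decide which set receives the intervention, so that a child's arm is a human choice. The text does not support this. Children are randomised centrally to the two arms before the interventions start, what trainers receive is the result of that randomisation, and the randomisation administrator also knows which intervention each group code stands for. That fits an arm already fixed for each group of children, with the trainer choosing which arm to lead. Whether trainers choose before or after the email is not stated. Choosing with knowledge of who is in each group is possible but not shown, and even then the children's arms would stand. Nor does the email expose allocation at enrolment: site investigators obtain consent, and randomisation follows the baseline assessment.

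Other mitigations are real. All trainers are trained in both programmes, which are manualised, supervised and audiotaped with blinded review of protocol violations. The switch gives each trainer both arms under the four-group plan, and it does not need equal sizes everywhere, only a match between each trainer's own two groups. A systematic bias needs centres to sort mostly in one direction and block sizes to differ in a consistent way, and nothing in the article suggests either. The therapist random-effect model also covers the primary outcome.

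This limits the size of the problem but does not remove it. Order is still self-selected, balance is not guaranteed, and the therapist-adjusted model is not the confirmatory test. In a centre with only a first block, that model also has no within-trainer comparison of the arms to work with.

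**Conclusion.** The point holds in limited form. The order in which trainers deliver the arms is chosen by the trainers, not randomised, and the primary ANCOVA does not adjust for trainer. The central randomisation of children is not called into question.

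The size of any bias cannot be derived from the documents. At an assumed trainer difference of 0.2 SD it is 0 with equal blocks, 0.09 SD with groups of 8 then 3, and 0.20 SD where only the first block runs. These figures assume two trainers per centre and all centres sorting the same way. Mixed sorting, or a single closed centre, brings the trial-wide figure down to a few hundredths of an SD. The expected effect is modest, but the source of bias is avoidable and the article gives no reason for allowing the choice.

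**What to change.** - **Replace the choice.** In the Randomization section, for blocks not yet started, have the central office draw at random within each centre which trainer leads which arm first, reversed in the next block. Fix the draw before any allocation result is released to trainers, and cover groups beyond the fourth by the same rule.
- **Centres already under way.** Where a first block has already been run by choice, keep the switch for the second block, since a fresh draw there could undo the balance. Document who chose what and, if known, whether this was before or after the allocation results arrived.
- **Clarify the wording.** State that the arm of each group of children is fixed centrally and that only the leading trainer is being assigned.
- **Analysis.** Report the therapist-adjusted model of the primary endpoint as a named sensitivity analysis beside the ANCOVA. The mixed model is already planned, so this needs no new data. With about ten trainers, its therapist variance will be imprecise.

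The cost is a short text change, one random draw per centre and slightly less scheduling freedom for trainers.
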